| Background and rationale | 6a | 
Description of Research Question and Justification
 
The primary research question for this study is: "Can the act of kissing accelerate the recovery of salivary pH after consuming acidic beverages compared to the natural recovery process?"
 
Rationale for the Study:
 
This study is motivated by the increasing prevalence of dental caries worldwide, largely influenced by frequent exposure to dietary acids, which lower salivary pH and demineralize enamel. Previous studies have explored various methods to restore salivary pH, such as the use of mouth rinses, chewing gum, and dietary interventions. However, no research has yet evaluated the potential protective effect of kissing—a natural and common behavior—on salivary pH recovery.
 
Summary of Relevant Studies:
 
 
1. Acidic Beverage Impact on Salivary pH: Studies have shown that beverages like sodas and citrus-based drinks significantly reduce salivary pH, which can persist for up to 40 minutes, creating a window of susceptibility for enamel erosion and caries development.
 
2. Kissing and Salivary Exchange: Limited literature suggests that kissing facilitates salivary exchange, which may dilute acidic components and introduce buffering agents from one partner's saliva, potentially aiding in faster pH recovery.
 
3. Gaps in Current Knowledge: While previous research has focused on artificial interventions, the natural interaction between two individuals during a kiss has not been studied, leaving a gap in understanding its potential health benefits.
 
 
This study aims to address this gap by systematically evaluating the effect of kissing on salivary pH recovery, with the goal of identifying a novel, accessible, and natural protective behavior against acidic challenges to oral health.
 |

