| Trial design                                              | 8  | 
The study will be a randomized controlled trial with parallel groups. Participants will be randomly assigned to one of three groups:
 
 
○ Control group: Participants who do not kiss after consuming an acidic beverage.
 
○ Experimental group 1: One member of the couple consumes an acidic beverage, and both partners kiss for 40 seconds.
 
○ Experimental group 2: Both members of the couple consume an acidic beverage and kiss for 40 seconds.
 
 
The results will be used to evaluate whether the act of kissing restores salivary pH more quickly than the time it takes for the body to do so physiologically. This design allows for clear comparisons of the effects of the different conditions, with an appropriate control group.
                                                                                                                                                                                                                                                                                                                                               |
| Methods: Participants, interventions, and outcomes |    |                                                                                                                                                                                                                                                                                                                                                                                                                                                                                                                                                                                                                                                                                                                                                                                                                                                                                                                                                                                                                                                                                                                                                                                                        |

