| Implementation                              | 16c | 
Implementation:
During enrollment, each participant pair will receive a unique code. These codes will be sent to [name], who will perform the randomization without access to any identifying information, ensuring impartiality. She will then relay the group assignments back to the study coordinator, who will oversee the implementation during the intervention phase. This process maintains the integrity of the randomization and minimizes potential biases.
                                                                                                                                                                                                                                                                                                                                                                                                                                                                                                                           |
| Blinding (masking)                          | 17a | 
Who Will Be Blinded:
This study will incorporate blinding at three levels to minimize bias and ensure the integrity of the results:
 
 
1. Participants: Participants will remain unaware of their group assignment (control or experimental) until the day of the experiment. This approach prevents anticipatory salivation or behavioral changes that could influence the results.
 
2. Investigators: The research team responsible for collecting and analyzing the data will not know the group assignments during the intervention phase. The assignments will only be revealed after data collection is complete to avoid any unintentional biases.
 
3. External Randomizer ([name]): [name], who performs the randomization process in Miami, USA, will be blinded to participant identities. She will only receive anonymized participant codes for allocation, ensuring impartiality in group assignments.
 
 |

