| Statistical methods | 20a | 
Analysis of Primary and Secondary Outcomes:
 
The primary outcome, the time required for salivary pH to return to neutral (pH 7.0), will be analyzed using appropriate statistical methods depending on the data distribution. First, tests of normality (e.g., Shapiro-Wilk test) will be conducted to determine if the data follows a normal distribution. If the data meets the assumptions for parametric tests, a one-way ANOVA will be used to compare the mean recovery times across the three groups: control, experimental group 1 (only one partner drinks the acidic beverage), and experimental group 2 (both partners drink the acidic beverage).
 
If the assumptions for ANOVA are not met, the non-parametric Kruskal-Wallis test will be applied to compare the groups. Post-hoc analyses (e.g., Tukey's HSD for ANOVA or pairwise comparisons with Bonferroni correction for Kruskal-Wallis) will be conducted to identify specific group differences.
 
For secondary outcomes, including salivary pH levels at specific time intervals, repeated-measures ANOVA will be used if the data meets parametric assumptions. Otherwise, the Friedman test will be employed to evaluate changes in pH over time within and between groups.
 
Additionally, pairwise comparisons will be performed to assess the differences in mean recovery times between the control group and each experimental group (control vs. experimental 1, and control vs.
                                                                                                                                                                                                                                                                                                                                                                                                                                                                                                                                                                                                                                                                  |

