|                            |     | experimental 2). These comparisons will utilize independent t-tests if parametric assumptions are met or Mann-Whitney U tests if they are not.                                                                                                                                                                                                                                                                                                                                                                                                                                                                                                                                                                                                                                                                                                                                                                                                                                                                                                                                                                                                                                                                                                                                                                                                                                                                                                                                                                                                                                                                                                                                                                                                                                                                                                                                                                                                                                                                                             |

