|                            | 20b | 
Missing data will be managed using the following approach:
 
 
1. Complete-Case Analysis: Only participants with complete data for the primary outcome will be included in the primary analysis.
 
2. Sensitivity Analysis: If more than 10% of the data are missing, sensitivity analyses will be conducted using multiple imputation methods to assess the robustness of the findings.
 
3. Documentation of Missing Data: All instances of missing data will be documented, and the reasons for missingness (if known) will be recorded in a study log.
 
                                                                                                                                                                                                                                                                                                                                                                                                                                                                                                                                                                                                                                                                                                                                                                                                                                                                                                                                                                                                                                                                                                                                                                                                                                                                                                                                                                                                              |

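### Item 20a names only tests for independent observations and never fixes the couple as the unit of analysis; if both Experimental group 2 drinkers are entered separately, tests involving that arm exceed 5%

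*Protocol*

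**What the plan says.** **Randomised unit.** Item 16c of the protocol assigns by couple: "each participant pair will receive a unique code", and that code is what is randomised.

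**Drinkers per couple.** Item 8 defines Experimental group 1 as "One member of the couple consumes an acidic beverage, and both partners kiss for 40 seconds" and Experimental group 2 as "Both members of the couple consume an acidic beverage and kiss for 40 seconds". For control, item 11a refers to a single drinker. So Experimental group 2 is the only arm with two recovery times per couple.

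**Unit of data and analysis.** Item 12 counts samples per participant. Item 19 gives each participant a code under which data are stored and analysed. Item 20b sets the analysis population: "Only participants with complete data for the primary outcome will be included in the primary analysis".

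**Sample size.** Items 2b and 10 plan 15 couples per group. Item 14 plans 10 participants per group, raised to 12.

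**Tests.** For the primary outcome, item 20a states that "a one-way ANOVA will be used to compare the mean recovery times across the three groups", with Tukey follow-up. If its assumptions fail, "the non-parametric Kruskal-Wallis test will be applied to compare the groups". For control against each experimental group, "These comparisons will utilize independent t-tests if parametric assumptions are met or Mann-Whitney U tests if they are not".

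**The concern.** Every test named in item 20a for recovery time treats each observation as independent of the rest. Two partners in Experimental group 2 are unlikely to be independent: the rationale in item 6a is that "kissing facilitates salivary exchange", so each partner's recovery should depend partly on the other's saliva.

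If both times go into the test as two separate observations, the Experimental group 2 mean is credited with more information than it holds. Its standard error is too small, its interval too narrow, and the three-group test and comparisons with that arm reject too often when there is no effect.

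The checks in item 20a do not protect against this. A Shapiro-Wilk test does not detect dependence between partners, and the rank-based alternatives assume independence too.

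**Working it through.** **1. The plan's own figure.** Item 14 uses f = 0.76, alpha 0.05, power 0.95 and three groups. With 30 participants the noncentrality is 30 × 0.76² = 17.3 on 2 and 27 degrees of freedom, and power is 0.950. Adding 20% gives 30 × 1.2 = 36. The figure reproduces, for equal groups of independent observations.

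**2. Standard error for Experimental group 2.** Let there be n couples per arm, unit variance per drinker and correlation ρ between partners. The mean over the 2n drinkers has variance (1 + ρ)/(2n); a test that ignores pairing uses 1/(2n). The true standard error of that mean is therefore √(1 + ρ) times the one used: 1.05 at ρ = 0.1, 1.22 at 0.5, 1.41 at 1. With n = 15, the 30 drinkers are worth 30/(1 + ρ) independent ones: 20 at ρ = 0.5 and 15 at ρ = 1.

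**3. Control against Experimental group 2.** The true variance of the difference is 1/n + (1 + ρ)/(2n), against 1/n + 1/(2n) as tested. With n = 15 and ρ = 0.5:

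- true: 0.0667 + 0.0500 = 0.1167
- as tested: 0.0667 + 0.0333 = 0.1000
- ratio 1.167, so the standard error is √1.167 = 1.080 times the one used, an understatement of 1 − 1/1.080 = 7.4%
- actual level of a two-sided 5% z-test: 2 × [1 − Φ(1.96/1.080)] = 7.0%

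At ρ = 0.8 the understatement is 11.1% and the level 8.2%.

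**4. Simulation with no true effect.** Normal outcomes, 15 / 15 / 30 drinkers, 40,000 runs (20,000 for Kruskal-Wallis); rejection rates at nominal 5%:

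| ρ | ANOVA | Kruskal-Wallis | Control vs Exp. 2, t-test |
|---|---|---|---|
| 0 | 5.0% | 4.8% | 4.9% |
| 0.1 | 5.4% | 5.2% | 5.3% |
| 0.3 | 6.4% | 5.8% | 6.3% |
| 0.5 | 7.0% | 6.7% | 7.0% |
| 0.7 | 8.3% | 7.6% | 8.1% |
| 0.9 | 9.3% | 8.9% | 9.1% |
| 1.0 | 10.0% | 9.2% | 9.7% |

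A separate run of 20,000 trials gave ANOVA rates of 5.7%, 7.2% and 8.8% at ρ = 0.2, 0.5 and 0.8. Rates were much the same when outcomes were put on a 5-minute grid capped at 40 minutes, as item 12 would record them.

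**5. Other readings of the size.** With 12 couples per arm (12 / 12 / 24 drinkers) the ANOVA rate is 5.5% to 9.9% for ρ from 0.1 to 1. If 12 per group in item 14 means six couples in Experimental group 2 (12 / 12 / 12 drinkers), it is 5.4% to 11.3%.

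**6. One value per couple.** With the couple mean in Experimental group 2 and 15 values per arm, ANOVA rejects in 5.0% to 5.2% and the control vs Experimental group 2 t-test in 4.9% to 5.1% at every ρ from 0 to 1. A couple mean has variance (1 + ρ)/2 against 1 for a single drinker, so an unequal-variance comparison is the safer choice, above all if arms differ in size. With 12 / 12 / 6 values, the pooled t-test falls to 3.0% at ρ = 0 while the Welch test stays at 4.8% to 5.1% over the whole range.

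**The case against.** The protocol never says outright that both Experimental group 2 partners enter the primary test separately. The word participant is also used loosely: item 16a randomises participant codes that, by item 16c, belong to pairs, so its use in item 20b cannot settle the matter alone. Items 2b and 10 count couples, and one recovery time per couple would give 15 equal-sized values per arm, above the 12 in item 14. One-way ANOVA on those values would be valid as item 20a words it, and a statistical analysis plan might say so.

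This stands to the extent that the finding must be conditional. It does not remove the point. Items 12, 19 and 20b together make separate entry the natural reading, no text selects one partner or averages the two, and the protocol does not leave the tests open: it names them. The conflict between couples and participants in the sample size is itself in the text.

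The size is also fairly disputed. Item 6a describes the benefit of exchange only as possible, and nothing supports a particular correlation after a 40-second kiss and 40 minutes of recovery. Shared calibration adds little, since item 18a calibrates per session and not per couple. Hence the range above instead of a single figure.

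A reader might infer that both partners are analysed in every arm, which would inflate the error much more. The documents do not support that: by items 8 and 11a the second partner in control and Experimental group 1 does not drink, so has no recovery time after a drink.

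**Conclusion.** The protocol fixes the unit of analysis badly: it randomises couples, describes data and analysis by participant, counts the sample both ways, and names only tests that assume independence. If both Experimental group 2 times are entered separately, the three-group test has a true level of about 5.7% at a within-couple correlation of 0.2, 7% at 0.5, 9% at 0.8 and at most about 10%, with 15 couples per arm. Comparisons of Experimental group 2 with either other arm are affected in the same direction. The direction holds for any positive correlation; the size rests on an assumed correlation and a simplified outcome model.

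It would be wrong to conclude that every comparison fails. The t-test of control against Experimental group 1 uses one drinker per couple and keeps its level. Nor do the documents show that the inflation is certain: with one index drinker or one couple mean in Experimental group 2 it disappears.

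**What to change.** In item 20a, state that the couple is the unit of analysis, in one of two ways:

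- one value per couple (in Experimental group 2, the mean of the two partners' outcomes), compared with methods that allow unequal variances; or
- a model on individual drinkers with a couple random effect, or couple-clustered standard errors, with a small-sample degrees-of-freedom correction.

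Apply the same rule to the analysis of pH over time. For rank-based tests, use one value per couple or permute group labels over couples. In item 20b, say how a couple is handled when only one Experimental group 2 partner has a complete outcome. State the sample size in couples, with the same number, in items 2b, 10 and 14.

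The cost is a few sentences and no new data. Intervals for Experimental group 2 become slightly wider: at a correlation of 0.5 the standard error of its difference from control rises by about 8% (the factor 1.080 above), which is the uncertainty already present. Fixing the rule before the data are seen also prevents the unit from being chosen by result.
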